## Abstract

**Background:**

A high proportion of the costs for respiratory diseases are generated by a relatively small group of patients with severe disease (recognized or unrecognized) or complex problems that include multimorbidity, at-risk behaviors, and socioeconomic disadvantage. These patients often struggle to engage with the structured, proactive, care approaches for chronic disease management advocated for asthma and chronic obstructive pulmonary disease (COPD), resulting in repeated emergency use of both primary and secondary health care. An integrated approach for the management of complex patients, incorporating both specialist and primary care teams’ expertise, may be effective in improving outcomes for such high-risk patients. However, the evidence is mixed, and there is a need for evaluation of models of integrated care in routine “real-world” clinical settings.

**Objective:**

This mixed-methods protocol examines the implementation of a novel integrated care model for patients with airways disease and undifferentiated breathlessness by using both quantitative and qualitative evaluation of processes, patient and health care professional experiences, and clinical outcomes throughout the clinic cycles. It aims to establish whether Modern Innovative Solutions to Improve Outcomes in Asthma, Breathlessness, and Chronic Obstructive Pulmonary Disease (MISSION ABC), including innovative diagnostic and self-management tools, can deliver improvements in health service use and clinical outcomes for the different patient groups (asthma, breathlessness, and COPD) and compares the 12-month period prior to the first patient visit and the 6-month period following the last visit.

**Methods:**

A combination of study designs is required to evaluate all aspects of the service: participatory action research approach, involving real-time evaluation at each clinic to inform subsequent clinics; before-and-after study for patient outcomes before and after clinic attendance; and qualitative methods (interviews and focus groups).

**Results:**

The results will be compiled and published in April 2019.

**Conclusions:**

Evaluation of the clinic cycles will include consideration of qualitative data from patients, carers, and health care professionals in addition to quantitative outcomes for service implementation and patient factors. The long-term impact of the service will be evaluated using clinical and health service outcomes.

**International Registered Report Identifier (IRRID):**

DERR1-10.2196/9228

## Introduction

### The Burden of Disease

Respiratory diseases are highly prevalent and a major cause of health care utilization in Wessex, United Kingdom. The two most common chronic respiratory diseases—asthma and chronic obstructive pulmonary disease (COPD)—are underdiagnosed, are major drivers to acute care episodes, and show poor clinical outcomes compared to other conditions in many areas of the region.

More than 1 million people in the United Kingdom are diagnosed with COPD. There is still a “prevalence gap” between the expected and actual prevalence of COPD among general practitioner (GP) practices, and in 13% of the UK population aged over 35 years, COPD is undiagnosed. These “missing millions” will likely need acute care, and 15% will only be diagnosed on admission to the hospital [1]. More than 5 million people are affected by asthma in the United Kingdom, and more than 500,000 people have severe or difficult-to-control asthma, of which 70% have an allergic subtype [2]. Patients with severe, exacerbation-prone disease are more likely to be admitted to the hospital and account for the most significant utilization of health services. Both COPD and asthma are associated with increased morbidity and mortality and can lead to disabling symptoms that impact the patient’s quality of life and well-being. COPD is the fifth most common cause of death in the United Kingdom, resulting in approximately 25,000 deaths annually. It is also the second most common cause for hospital admission in the United Kingdom, and 35% of patients are readmitted within 30 days. In 2009, asthma accounted for 1,131 deaths in the United Kingdom, triggering a National Audit of Asthma Deaths. The National Review of Asthma Deaths [3] published in 2014 concluded that many areas in the diagnosis and care of patients with asthma such as access to timely and appropriate care, use of personalized action plans, and appropriate severity assessment can be improved to reduce unnecessary deaths.

The National Health Service spends £2 billion per year on the management of asthma and COPD [4]. Both conditions have direct financial costs, additional social costs through time off work and reduced productivity, and further indirect costs through reduced quality of life and well-being. The annual health care expenditure on COPD is more than £800 million (£1.3 million per 100,000 population). The treatment of severe, exacerbation-prone COPD (exacerbation is defined as an acute worsening of respiratory symptoms requiring an increase in therapy [5]) costs ten times more than that of mild disease. COPD is responsible for 24 million lost working days annually, costing the economy £2.7 billion. Nearly 80% of costs for asthma are related to the treatment of poorly controlled disease [6], which amounts to over £1 billion per annum [2] as a direct cost and £6 billion as an indirect cost to society (time off work and lost productivity). Four of the top 10 most expensive drugs covered by the National Health Service are inhaled medications for asthma and COPD.

Shortness of breath is recorded in 1% of primary care consultations [7] and 10% of the population affected by chronic breathlessness symptoms [8]. This proportion increases to one-third in the elderly, with a significant impact on the functional status and health-related quality of life [9]. Although breathlessness is a symptom of many diseases, the referral and management systems are often specific to the diagnosis. Thus, patient visits to more than one outpatient department for breathlessness may result in an onerous clinical journey and underrecognition of comorbidity [10].

### A New Model of Care

A high proportion of the costs for respiratory diseases is generated by a relatively small group of patients with severe disease (recognized or unrecognized) or complex problems that include multimorbidity, at-risk behaviors, and socioeconomic disadvantage. Such patients often struggle to engage with the structured, proactive care approach to chronic disease management advocated for asthma and COPD, resulting in repeated emergency health care use of both primary and secondary care. An integrated approach for the management of complex patients, incorporating both specialist and primary care teams’ expertise, may be effective in improving outcomes for such high-risk patients. However, the evidence is mixed, and there is a need for evaluations of models of integrated care in routine “real-world” clinical settings.

The Modern Innovative Solutions Improving Outcomes in Asthma, Breathlessness, and COPD (MISSION ABC) system is a new model of care that starts by identifying at-risk patients and subsequently streamlines their care, incorporating new technology to improve management of airways disease. Patients are identified using criteria that indicate poor disease control, a heavy burden of symptomatology, or unidentified disease. The patients are then delivered streamlined assessment and care in a one-stop (MISSION Rapid) or two-stop clinic journey (Rapid plus MISSION Investigation clinics). MISSION Rapid clinics, organized in the community, promote integration of primary and specialist teams, wider respiratory multidisciplinary teams, psychological and well-being services, charity, and patient group representation. Each patient’s diagnosis is reviewed using spirometry, fractional exhaled nitric oxide (FeNO), and oscillometry (each provided by a specialist respiratory physiologist) along with a specialist medical review; the reasons for poor disease control are explored (unidentified comorbidity, difficulties in self-management, coexisting anxieties, or social stressors), and the medications are optimized using local and national guidelines. All patients were offered personalized self-management plans. Patients who are stable are supported in the management of their disease through education (myCOPD [11] or myAsthma [12]) and upskilling of lead health care professionals (HCPs) and champions in GP practices through competency-based training, including spirometry and comorbid disease management. The model of patient flow through the MISSION service is shown in Figure 1 (COPD), Figure 2 (asthma), and Figure 3 (breathlessness).

**Figure 1 figure1:**
[figure not shown]
COPD cohort flow chart with study outcomes shown in yellow boxes. COPD: chronic obstructive pulmonary disease; GRASP: Guidance on Risk Assessment in Stroke Prevention; CAT: COPD Assessment Test; ASK-12: Adherence Starts with Knowledge questionnaire-12; PAM: Patient Activation Measure; WBPA: weight-bearing physical activity; MDT: multidisciplinary team; GP: general practitioner; PIS: patient information sheet; HCP: health care professional; BMI: body mass index; SF-36: Short Form Health Survey-36; VSAQ: Veterans Specific Activity Questionnaire; EQ5d: EuroQoL-5D; WPAI: Work Productivity and Activity Impairment.

**Figure 2 figure2:**
[figure not shown]
Asthma cohort flow chart with study outcomes shown in yellow boxes. GRASP: Guidance on Risk Assessment in Stroke Prevention; CAT: Chronic obstructive pulmonary disease Assessment Test; ASK-12: Adherence Starts with Knowledge questionnaire-12; PAM: Patient Activation Measure; WBPA: weight-bearing physical activity; MDT: multidisciplinary team; GP: general practitioner; PIS: patient information sheet; HCP: health care professional; BMI: body mass index; EQ5d: EuroQoL-5D; WPAI: Work Productivity and Activity Impairment; ACQ: Asthma Control Questionnaire; TLA: temperature-controlled laminar airflow.

**Figure 3 figure3:**
[figure not shown]
Breathlessness cohort flow chart with study outcomes shown in yellow boxes. COPD: chronic obstructive pulmonary disease; GRASP: Guidance on Risk Assessment in Stroke Prevention; CAT: COPD Assessment Test; ASK-12: Adherence Starts with Knowledge questionnaire-12; PAM: Patient Activation Measure; WBPA: weight-bearing physical activity; MDT: multidisciplinary team; PIS: patient information sheet; HCP: health care professional; BMI: body mass index; SF-36: Short Form Health Survey-36; VSAQ: Veterans Specific Activity Questionnaire; EQ5d: EuroQoL-5D; WPAI: Work Productivity and Activity Impairment.

### A New Service for Asthma Patients

We will implement a novel clinical pathway for asthma patients that includes diagnosis, assessment, and adjustment of treatment; maintains control using complementary innovations and models of care; and draws on resources and skills from primary, secondary, and tertiary care.

We will use Guidance on Risk Assessment in Stroke Prevention (GRASP) [13] searches across Wessex Clinical Commissioning Groups to identify patients who are likely to have asthma. When a diagnosis is established, we will identify patients whose conditions are not well controlled (eg, frequent exacerbations, emergency department visits, hospital admissions, use of three or more controller medications, and use of frequent short-acting bronchodilators). These patients’ records will be reviewed by specialist nurses and, if appropriate, in MISSION clinics. The clinics will provide timely diagnosis with cutting-edge technology, including FeNO and airway oscillometry, assessment of disease control and comorbidity, an education session, and a self-management plan through written and mobile- or Web-based solutions, where appropriate. Inhaler technique and adherence will be assessed, and patients will be encouraged to maintain good practices with the Flo-Tone device and inhaler-use monitor [14]. Patients requiring more urgent care will be assessed and treated by a rapid response team.

After the patients visit the MISSION Asthma clinic, the following tools will be used to enable continuous assessment, adjustment, and maintenance of disease control: Message Dynamics portal [15], Clinitouch system [16,17], myAsthma, Airsonett [18,19], smoking cessation, and education. Message Dynamics and Clinitouch use communications technology across multiple platforms to monitor symptoms, allowing early recognition of deterioration. By combining these approaches, HCPs can target patients early in an exacerbation event by using community-based management, thereby reducing the need for admission and the cumulative burden of symptoms on the patient. MyAsthma is a self-management online platform providing education and a symptom diary to encourage patients to manage their asthma. The Airsonett device is a laminar airflow device that reduces allergen exposure in patients with severe allergic asthma and may increase control and reduce healthcare utilization.

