### Aims and Objectives

This study aimed to examine (1) the implementation of a novel integrated care model for patients with airways disease and undifferentiated breathlessness using both quantitative and qualitative evaluation of processes and patient and HCP experiences and (2) clinical outcomes throughout the clinic cycles driving a continuous improvement process, evaluated through participatory action research. We also aimed to establish whether MISSION ABC, including innovative diagnostic and self-management tools, can deliver improvements in health service use and clinical outcomes for different patient groups (asthma, breathlessness, and COPD) by comparing the 12-month period prior to the first patient attendance and the 6-month period following attendance, by using regressional analyses to control for seasonal variation bias.

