#### Overall Description of Study Participants

Adult patients (aged ≥ 16 years) with poorly controlled asthma or COPD as well as those with undifferentiated breathlessness will be identified using GRASP tools; referred from a community pharmacist or by their primary care team; and invited to a local MISSION clinic with a relative, friend, or carer in attendance, if they wish. All eligible attendees will be invited to participate in the study. The sample size will be determined by the uptake of appointments and clinic capacity but is projected to be 500 patients and 15 HCPs.

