#### Randomization

There will be no randomization.

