#### Analysis of Quantitative Outcome Data

The objective of all analyses is to examine differences in measured variables between time points.

The following comparisons will be made:

Asthma Control Questionnaire, CAT, and AQLQ: baseline as compared to 3 and 6 monthsEmergency care outcomes: 3 and 6 months prior to study as compared to the 3- and 6-month study periodActivation or medicine compliance (ASK-12 and Patient Activation Measure): baseline as compared to 3 and 6 monthsEuroQoL-5D and weight-bearing physical activity: baseline as compared to 3 and 6 months

All the abovementioned variables are continuous measures. Comparisons between time points will be made using the paired *t* test or the Wilcoxon matched-pairs test, depending on the distribution of the changes in outcome between time points.

Summaries of the measures of monitoring and supported follow-up will be prepared (measures outlined above). Patient satisfaction measures will be summarized descriptively. Numbers and percentages will be used for categorical variables, whereas mean and SD or median and interquartile range will be used for continuous variables. Uncertainty in percentages, means, and medians will be quantified by calculating the appropriate 95% CIs.

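### Asthma (and perhaps COPD) patients are picked partly for high emergency use, which is then the outcome of an uncontrolled before-after test, so part of any fall is expected from regression to the mean

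*Protocol article*

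**What the plan says.** **Selection.** Under A New Service for Asthma Patients: "we will identify patients whose conditions are not well controlled (eg, frequent exacerbations, emergency department visits, hospital admissions". The same list goes on to controller medication and short-acting bronchodilator use, and a nurse record review follows. No look-back period is given. For the whole service, A New Model of Care says "Patients are identified using criteria that indicate poor disease control, a heavy burden of symptomatology, or unidentified disease". Overall Description of Study Participants covers adults "with poorly controlled asthma or COPD as well as those with undifferentiated breathlessness will be identified using GRASP tools", and also allows referral by a community pharmacist or the primary care team.

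**Outcomes.** Patient and Health Service Use Outcomes lists unscheduled care, and exacerbations in the 6 months on either side of attendance. The section on disease control and activation measures records unscheduled care, steroid or antibiotic courses and admissions at 3 and 6 months, against the previous 6 and 12 months.

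**Comparison.** Analysis of Quantitative Outcome Data sets emergency care in the 3 and 6 months before against the 3 and 6 months of study, using a paired t test "or the Wilcoxon matched-pairs test, depending on the distribution of the changes in outcome between time points". Aims and Objectives instead describes "comparing the 12-month period prior to the first patient attendance and the 6-month period following attendance". The one adjustment for bias that the article names stands in the same section and concerns season: "by using regressional analyses to control for seasonal variation bias". The Randomization section reads "There will be no randomization". No comparison group is named for these outcomes.

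**Claim.** The aim is to establish whether the service "can deliver improvements in health service use and clinical outcomes for different patient groups".

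**The concern.** If a patient enters because a count was high, the count in the same months overstates that patient's usual rate. The next period is lower on average with no intervention at all. A one-group paired test attributes the whole difference to the service. Seasonal regression corrects for time of year, not for selection at a high point.

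The Discussion says the results will inform decisions on future service implementation. A fall in emergency use that an ineffective service would also show is a poor basis for that.

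**Working it through.** The article gives no event rate, dispersion, selection threshold or look-back, so there is no figure to reproduce. The check asks how large a fall appears when the true effect is zero.

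**Assumptions (none from the document).** Each patient has a constant yearly rate drawn from a gamma distribution with mean m and shape k. Counts are Poisson and independent between periods. The service has no effect.

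**1. Selection on at least one event in the 6 months ending at the clinic.** Let μ = m/2 and p0 = (k/(k+μ))^k, the chance of no event in 6 months.

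- Before: B = μ/(1−p0)
- After: A = [μ − p0·kμ/(k+μ)]/(1−p0)
- Spurious fall: f = 1 − A/B = (k/(k+μ))^(k+1)

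| m per year | k = 0.5 | k = 1 | k = 2 |
|---|---|---|---|
| 1 (μ = 0.5) | 0.500^1.5 = 35% | 0.667^2 = 44% | 0.800^3 = 51% |
| 2 (μ = 1) | 0.333^1.5 = 19% | 0.500^2 = 25% | 0.667^3 = 30% |

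At m = 1, k = 1, the 6-month mean goes from 1.50 to 0.83.

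**2. Selection on at least c events in 12 months.** At m = 1, k = 1, c = 2, E[X | X≥2] = 3, so 6-month before = 1.50. After = ½·(1+3)/(1+1) = 1.00, a fall of 33%. Over m = 0.5 to 2, k = 0.5 to 2 and c = 1 to 3, the fall runs from 9% to 68%.

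**3. Only a share q of patients selected on use** (case in step 2; the others have 0.50 before and after).

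- q = 0.5: 1.00 to 0.75, fall 25%
- q = 0.25: 0.75 to 0.625, fall 17%

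Share of 500 simulated null trials in which the paired t test gives p < 0.05 (167 is about one third of the projected 500):

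| q | n = 100 | n = 167 | n = 500 |
|---|---|---|---|
| 1 | 91% | 99% | 100% |
| 0.5 | 51% | 72% | 99% |
| 0.25 | 20% | 30% | 70% |
| 0 | 5% | 6% | 6% |

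**4. A wait of w months between identification and clinic.** The 6 months before the clinic then hold 6−w look-back months and w clean ones, so the fall is (6−w)f/(6−wf).

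- Step 1 with w = 2: f = 0.192 gives 0.770/5.615 = 14%, and f = 0.512 gives 2.048/4.976 = 41%.
- Step 2 (f = 0.333), simulated with n = 167 and all selected on use: gaps of 1, 3 and 6 months give falls of 29%, 20% and 0%, and rejection in 95%, 59% and 5% of runs.

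**5. Is a fixed baseline of months −12 to −6 before the clinic enough?** Not if patients wait. With a 6-month look-back, w of those six months still lie in the look-back, and the fall is wf/[6 − (6−w)f].

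- w = 2: 0.385/5.230 = 7% to 1.024/3.952 = 26%
- w = 3: 0.577/5.423 = 11% to 1.536/4.464 = 34%

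A baseline that ends before the look-back, counted from the identification date, has the same expected rate as the months after, so the fall is 0 under this model.

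**The case against.** Four objections have force.

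- **The overlap is inferred.** A reader might take the article to say that recent events select the patient and that the same months form the baseline. It does not; no look-back is given, and a condensed article may leave that to the full protocol. But events found in records precede attendance, and every stated 'before' window runs back from the clinic for 3 to 12 months. Overlap is probable, and nothing stated prevents it.
- **The explicit criteria are for one cohort.** Exacerbations, emergency visits and admissions are examples, given for asthma only. The COPD section states no use criterion for entry; prior health care use appears there only for choosing who is offered remote monitoring. For COPD the link rests on the general description of poor control. Breathlessness patients are found by a symptom without a diagnosis. It would be wrong to read the bias as equal across cohorts.
- **Near-certain significance at 500 patients does not follow.** The 500 is a projection over all three groups, while the aim is by group. With a quarter selected on use and 167 patients, the test rejects in about 30% of null runs.
- **The design is openly before-and-after.** The Study Design summary calls the work predominantly participatory action research accompanying a quality-improvement project. That supports descriptive reporting. It does not support the causal wording of the aim, and the summary's exploratory label covers only the innovations.

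**Conclusion.** The concern holds for asthma and possibly for COPD, and less for breathlessness. Variables used to find patients are later outcomes, the 'before' period runs up to the clinic, there is no comparison group, and seasonal adjustment does not address the problem. Part of any fall in emergency use should be expected without a service effect.

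The direction is well supported, given a probable overlap of windows. The size is not. The range of about 19% to 51% rests on assumed means of 1 to 2 events a year, shapes of 0.5 to 2 and every patient selected on at least one event in the last 6 months. It shrinks with partial selection or a wait and vanishes if the windows do not overlap. The document does not support a claim that any observed fall is entirely artefact.

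**What to change.** In Analysis of Quantitative Outcome Data, for patients identified by use-based criteria:

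1. State the look-back and use each patient's identification date. Take baseline use as a rate per person-month from the 12 months already collected, excluding the look-back counted back from identification, not from the clinic.
2. Report separately the rate between identification and first attendance, when selection has ended and the service has not begun.
3. If patients booked into later clinics serve as a concurrent comparison, use only their months after identification and before their own clinic. Earlier months contain their own selecting events and would bring back the spurious fall of step 1 in full.
4. Where no clean period exists (a look-back covering all 12 months, or referred patients with no defined look-back), report the paired change as descriptive and do not claim to establish that the service delivers improvements.

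**Cost.** The Results section says enrollment is complete and analysis is underway, so this changes analysis and wording only. It needs the identification date from the GRASP or referral list, which I assume was kept. Baseline person-time falls: with a 6-month look-back and a 2-month wait, 12 − 6 − 2 = 4 clean months remain. Those months, −12 to −8, match the calendar months of the first 4 after the clinic, which also helps with season. The apparent effect will probably be smaller.
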